### Sample size

2.4

Given that no comparative trials analyzing the therapeutic effect of PAP on reduction of grief symptoms has been published to date, sample size was calculated based on the results of González et al. (35) observational study. The observed Cohen’s d (0.84) for the study group between the baseline and the 15^th^-day-post-treatment assessment, and TRIG measurement correlation of 0.55, were used to estimate the sample size for this study. Therefore, sample size was calculated based on the assumption of a between groups differences at post-treatment of at least 9.4 points (TRIG score) in mean change between the A-MR and the NT groups. Sample size with power of 0.90 and an alpha of 0.05 was calculated using pwrss R package version 0.3.1 (58). To find at least the above effect size, a total sample of 69 participants is needed, but as drop-out rate of 20% were considered, 84 participants will be recruited.

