Despite the promising outcomes reported in the treatment of several mental health issues, no controlled studies have been conducted testing the efficacy of PAP for PGD, nor have any evaluated PAP’s potential in preventing prolonged grief when administered in the early course of bereavement. Previous observational research, however, has suggested that the ceremonial use of ayahuasca has therapeutic value in reducing the severity of grief (34–36). We therefore propose that ayahuasca assisted with an evidence-informed therapeutic approach, the meaning reconstruction model (37, 38), could show greater reduction in grief severity than psychotherapy alone.

The rationale behind this hypothesis is grounded in a wide range of neurobiological and psychological evidence. Ayahuasca is an Amazonian concoction, usually prepared from the *Banisteriopsis caapi* vine and the *Psychotria viridis* shrub, which has been utilized for healing and ritual purposes since pre-Columbian times (39). Regarding the neurobiological evidence, *in vitro*, animal and human studies have demonstrated how harmine, tetrahydroharmine, harmaline (all three present in *B. caapi*) and dimethyltryptamine (present in *P. viridis*) stimulate adult neurogenesis and neuroplasticity, similarly to other serotoninergic psychedelic substances (40–43). A window for neuroplastic changes would appear to open a few hours after administration, lasting from a few days to a month (44). This period has been related to improvement in grief, depressive mood, stress, mindfulness, acceptance, emotion regulation, social behavior, wellbeing, and quality of life (45). Moreover, elevated peripheral Brain-Derived Neurotropic Factor (BDNF) levels have been observed in healthy volunteers and clinically depressed patients two days following the ayahuasca administration, correlating with clinical improvement in those who were diagnosed with major depression (40). Recent studies have shown that psychedelics reopen a critical period to induce metaplasticity, which dynamically regulates the potential for synaptic plasticity (46, 47). This critical period is context-dependent and has been linked to the ability to induce social reward learning, psychological flexibility, cognitive reappraisal and new patterns of behavior (46, 48, 49). In sum, these studies highlight the importance of the post-treatment integration period to maximize the therapeutic effect of psychedelics.

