### Study design and hypotheses

2.1

This three-arm, non-randomized controlled trial investigates the efficacy of Ayahuasca-assisted Meaning Reconstruction therapy (A-MR) in decreasing normal and pathological grief symptoms in people who have lost a first-degree relative within the prior 12 months. Participants are sequentially allocated to the following treatment conditions: (1) a control group receiving Meaning Reconstruction therapy (MR), (2) a control group receiving No Treatment (NT), and (3) an experimental group receiving Ayahuasca-assisted Meaning Reconstruction therapy (A-MR).

The objective of this trial is two-fold. First, our aim is to compare the efficacy of A-MR with that of MR and NT by assessing differences in (a) the severity of normal grief symptoms, (b) pathological grief symptoms, (c) quality of life, and (d) posttraumatic growth. Moreover, we are also interested in analyzing how each condition may influence the proposed processes of change: (e) meaning-made (f) psychological flexibility, and (g) self-belief consistency. Additionally, we will explore the participants’ (h) subjective effects of ayahuasca and the (i) acceptance-avoidance promoting effects.

The following hypothesis will be tested:

Hypothesis 1. The experimental group receiving A-MR will show greater improvement in normal and pathological grief symptoms, quality of life, and post-traumatic growth compared to both control groups (MR and NT), at post-treatment and 3 months follow-up. Moreover, MR group will show greater improvement than the NT group, expecting a medium clinical effect size.

Hypothesis 1.1. The experimental group receiving A-MR will show greater improvement in psychological flexibility, meaning-made, and self-believed consistency compared to both control groups (MR and NT), at post-treatment and 3 months follow-up. Furthermore, MR will also show greater improvement than the NT group, expecting a medium clinical effect size.

Hypothesis 2. Reductions in the severity of normal and pathological grief symptoms will be principally related to changes in meaning- made, but also to changes in psychological flexibility and self-belief consistency. Moreover, a stronger relationship between changes in the severity of grief symptoms and meaning-made is expected in the A-MR group.

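### Section 2.4 takes one group's pre-post change as the A-MR minus NT difference with no allowance for improvement under NT, and H1's two contrasts involving MR have no stated power

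*Protocol article*

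**What the plan says.** Section 2.4 notes that no comparative trial was available, so "sample size was calculated based on the results of" an observational study. The effect size, d = 0.84, was observed "for the study group between the baseline and the" day-15 assessment. This d and a "TRIG measurement correlation of 0.55, were used to estimate the sample size for this study". The next sentence draws from them "the assumption of a between groups differences at post-treatment of at least 9.4 points (TRIG score) in mean change between the A-MR and" NT groups. With power 0.90 and alpha 0.05 this gives 69 participants, and the Abstract sets at least 23 per arm.

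The hypotheses go beyond A-MR vs NT. H1 in section 2.1 has A-MR improving more than both control groups, and adds that the "MR group will show greater improvement than the NT group, expecting a medium clinical effect size". The rationale in section 1.1 is that ayahuasca with MR therapy "could show greater reduction in grief severity than psychotherapy alone". Section 2.6 applies Bonferroni corrections to all analyses. Its only power statement concerns the mediation models.

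**The concern.** A pre-post change in one group mixes the treatment effect with whatever would have happened anyway. A difference in change between two arms removes the second part. Carrying the first quantity over as the second, with no deduction, leaves no room for improvement under NT unless A-MR does better than the source group by the same amount.

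The article gives reasons to expect NT scores to fall. Section 2.2 requires a loss within the past 12 months and TRIG of 40 or more, and TRIG is also a primary outcome. The introduction describes grief as a natural process. NT is followed over the time of nine weekly sessions and then for 3 months, against 15 days in the source.

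The contrast that isolates ayahuasca is A-MR vs MR, and it is not sized at all. If its power is low, a non-significant result says little, yet it could be taken as evidence that ayahuasca adds nothing.

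**Working it through.** **Inputs.** From section 2.4: d = 0.84, correlation 0.55, difference 9.4 points, power 0.90, alpha 0.05, total 69 (23 per arm). Assumed, because the article gives no figure: NT improvement of 2, 3 or 4 points, and a medium effect of 0.5 SD for MR vs NT.

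**Implied SDs.**
- Raw SD = 9.4 / 0.84 = 11.19
- Change-score SD = 11.19 × √(2 × (1 − 0.55)) = 10.62
- Baseline-adjusted SD = 11.19 × √(1 − 0.55²) = 9.35

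**Reproducing 69.** The standardised effect on change scores is 9.4 / 10.62 = 0.885. A two-sample t-test (noncentral t) at one-sided alpha 0.05 has power 0.893 with 22 per arm and 0.905 with 23. Hence 23 × 3 = 69, an exact match, with the full 0.84 entered as the between-group effect. Two-sided, the same test needs 28 per arm. The article does not state sidedness for this calculation, so each basis below has its own reference row.

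**A-MR vs NT at 23 per arm.** The source change is held at 9.4 and the assumed NT improvement is subtracted.

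| NT improvement | Net difference | One-sided, change score | Two-sided, change score | Two-sided, baseline-adjusted |
|---|---|---|---|---|
| 0 | 9.4 | 0.905 | 0.84 | 0.92 |
| 2 | 7.4 | 0.75 | 0.64 | 0.75 |
| 3 | 6.4 | 0.64 | 0.52 | 0.62 |
| 4 | 5.4 | 0.52 | 0.39 | 0.48 |

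The effect of NT improvement is read down a column. The step from 0.905 to 0.84 in the top row is due to sidedness alone and is a separate matter.

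**MR vs NT.** 0.5 × 11.19 = 5.6 points. Two-sided power is 0.42 (change score) to 0.51 (adjusted), or 0.25 to 0.33 at 0.05/3.

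**A-MR vs MR, two scenarios, two-sided.**
- If 9.4 is the total A-MR vs NT effect, the gap is 9.4 − 5.6 = 3.8 points. Power is 0.22 (change score) to 0.27 (adjusted).
- If the source change reflects ayahuasca without MR therapy and the two effects add, MR cancels. The gap is then 9.4 less the part of the source change that was natural course: 7.4, 6.4 or 5.4 points for 2, 3 or 4. Power is 0.64, 0.52 or 0.39 (change score), or 0.75, 0.62 or 0.48 (adjusted).

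**Precision of A-MR vs MR.** The expected 95% CI half-width is 2.015 × SD × √(2/23). This is 6.3 points for change scores and about 5.6 baseline-adjusted.

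**The case against.** A reader might infer that the plan asserts untreated grief does not improve. It does not say so. It assumes a net difference of at least 9.4 points, which can also arise if NT improves and A-MR, with its nine therapy sessions, improves by more than the source group did. With additive effects and 2 to 4 points of natural course, A-MR vs NT would be 7.4 + 5.6 = 13.0 down to 5.4 + 5.6 = 11.0 points, above 9.4. This stands as a possibility. But section 2.4 does not argue it, so the figure is unjustified rather than shown to be wrong.

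A reader might also infer that the plan's own expectations imply a 3.8-point gap for A-MR vs MR. That is only one scenario. The article describes the source as research on ceremonial, naturalistic use and does not say that it included MR therapy. Even in the more favourable scenario, however, power for this contrast does not exceed 0.75 over the range considered.

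Table 1 lists TRIG at both enrolment and baseline. If these are separate measurements, some regression to the mean occurs before baseline. The natural course after a recent loss remains.

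The trial is called exploratory, sizing on one contrast is common, and the lack of comparative data is disclosed. Section 2.6 already plans between-group Cohen's d with 95% intervals, although not in TRIG points. No part of the article proposes reading a null A-MR vs MR result as no effect. These points limit the seriousness. They do not support an unqualified 0.90 when H1 states directional hypotheses to be tested.

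**Conclusion.** The concern holds in a limited form. The 0.90 applies to A-MR vs NT only, and only if the single-group change equals the net difference from NT. An assumed NT improvement of 2 to 4 points with no offset takes power on the reproducing basis from 0.905 to between 0.75 and 0.52. Two-sided, it falls from 0.84 to between 0.64 and 0.39 (change score), or from 0.92 to between 0.75 and 0.48 (adjusted). Neither MR contrast has stated power. MR vs NT is near 0.42 to 0.51 at 0.5 SD. A-MR vs MR lies between 0.22 and 0.75 depending on the scenario, which is too wide a range to treat that contrast as covered.

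These figures rest on an SD implied by 9.4 / 0.84 and on the assumed NT change and 0.5 SD. That 9.4 is the source change is itself inferred, from the wording of section 2.4 and the exact match to 69, because the source's point change and SD are not given.

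**What to change.** In section 2.4:
- State that 9.4 points is a single-group change taken as the net difference from NT, and that the 0.90 is conditional on this.
- Give power for NT improvements of 2 to 4 points, and say whether the test is one- or two-sided.
- State that A-MR vs NT is the only contrast sized for H1.
- Give power for MR vs NT, and for A-MR vs MR under both scenarios.

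In the analysis section, commit to reporting A-MR vs MR as a difference in TRIG points with its 95% CI (expected half-width about 5.6 to 6.3), and state that non-significance there will not be read as no added effect.

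This is a change of wording. It makes the stated power less favourable and needs no extra participants.

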### Data analyses

2.6

All the studied variables will be descriptively analyzed by means (SDs), medians (ranges) or n (percentages). Between groups baseline differences will be tested using 2-tailed t-test, Man-Whitney test or chi-square/Fisher’s exacts test based on the type of variables compared.

Despite the trial being exploratory study, data will be analyzed following the intent-to-treat and/or completer strategies, based on the presence of drop-out. The first hypothesis (H1) will be tested using an independent two-way repeated measures analysis of variance (ANOVA) with 3 levels for each factor (Group: A-MR *vs* MR *vs* NT; Time: pre-treatment *vs* post-treatment *vs* follow-up) and/or Linear Mixed Models (LMM) for each primary and secondary outcome studied. The LMM will be used to analyze the possible effect of between groups differences at baseline measures as covariables, and to analyze the effect of the presence PGD diagnoses following the ICD-11 duration criterion at baseline. Bonferroni corrections will be applied to all analyses, and partial eta-square and Cohen’s *d* effect sizes will be calculated for interaction effects and for between- and within-group comparisons, respectively. Confidence intervals for Cohen’s *d* will be estimated at a 95% confidence level and 500 bootstrap samples.

The analysis of the second hypothesis (H2) will be based on the outcomes of testing H1, with reduction in grief severity (TRIG and TGI scores) as the dependent variable for mediation analyses. The mediation model will include all participants in the study and will only incorporate the potentially significant mediating variables (meaning-made, psychological flexibility, and self-belief consistency) identified in previous analyses. Power analyses for the mediation models will also be conducted based on a Monte Carlo simulation.

The statistical analyses will be conducted using R version 4.2.3 (79). The following R packages will be used for data exploration, description, and preprocessing if necessary: tidyverse (80), car (81), moments version 0.14.1 (82), and nortest version 1.0-4 (83). The repeated measures ANOVAs and/or Lineal Mixed Models will be conducted using rstatix package version 0.7.2 (84). Finally, the mediation model will be tested using the lavaan package version 0.6-12 (85) and statistical power for the mediational analysis will be calculated using WebPower package version 0.9.4 (86).

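### The stated 0.90 power is for one contrast at an unadjusted alpha of 0.05, but the analysis section applies Bonferroni to all analyses; corrected power with 69 participants is lower by an amount the protocol leaves undefined

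*Protocol article*

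**What the plan says.** Section 2.4 (Sample size) takes its effect from an earlier observational study: Cohen's "d (0.84) for the study group between the baseline and the 15^th^-day-post-treatment assessment", with a "TRIG measurement correlation of 0.55, were used to estimate the sample size for this study". The target is a difference of "at least 9.4 points (TRIG score) in mean change between the A-MR and the NT groups" at post-treatment. The error rates are given as follows: "Sample size with power of 0.90 and an alpha of 0.05 was calculated using pwrss R package version 0.3.1". The result is that "a total sample of 69 participants is needed"; the abstract splits this as at least 23 per arm. With 20% drop-out allowed for, 84 are to be recruited. The section states neither the test, nor its sidedness, nor any adjustment for multiple comparisons.

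Section 2.6 (Data analyses) plans a 3 x 3 repeated-measures ANOVA and/or linear mixed models for each outcome and adds: "Bonferroni corrections will be applied to all analyses". It does not say over how many comparisons.

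Section 2.5.1 lists two primary outcomes, TRIG and TGI-SR. Hypothesis 1 in section 2.1 expects A-MR to do better "compared to both control groups (MR and NT), at post-treatment and 3 months follow-up", and also expects MR to do better than NT.

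**The concern.** The sizing spends the full 0.05 on one contrast, whereas the analysis section promises that the same contrast will be tested at a smaller alpha. Both statements cannot describe the same test, unless the Bonferroni family holds a single comparison. That is hard to square with three arms, two primary outcomes and a hypothesis naming three pairwise contrasts.

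At stake is how a negative result would be read. A trial described as 90% powered has a type II error of 0.10 for the effect it was sized on. If the corrected test has about 0.80 power, that error is about twice as large, and a null finding carries less weight than the protocol suggests. An undefined family also leaves room to choose the number of comparisons after the data are seen.

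**Working it through.** **Inputs.** From section 2.4: d = 0.84, correlation r = 0.55, difference 9.4 TRIG points, alpha 0.05, power 0.90, total 69. From the abstract: 23 per arm. Not stated, so assumed and varied here: the test, its sidedness and the number of comparisons m. The implied SD is 9.4/0.84 = 11.19.

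**Standardised effects.**
- Change score: SD = 11.19 x sqrt(2(1 - 0.55)) = 10.62, so d = 9.4/10.62 = 0.885.
- Baseline-adjusted: SD = 11.19 x sqrt(1 - 0.55^2) = 9.35, so d = 9.4/9.35 = 1.006 from unrounded values.
- 3 groups x 2 times interaction: f = 0.84/4 = 0.21.

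**Power formulas.** For the two-arm tests, noncentral t with 2 x 23 - 2 = 44 degrees of freedom and noncentrality d x sqrt(23/2): 3.00 for the change score and 3.41 baseline-adjusted. For the interaction, noncentral F with 2 and 66 degrees of freedom and noncentrality f^2 x N x 2/(1 - r) = 0.0441 x 69 x 2/0.45 = 13.52.

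**Reproducing the plan's figure at unadjusted 0.05.**
- Change score, one-sided: 23 per arm (69 in all), power 0.905.
- Interaction, 3 x 2: N = 68, rounded to 69 for equal arms, power 0.906.
- Baseline-adjusted, two-sided: 22 per arm (66) suffices; 23 per arm gives 0.916.
- Change score, two-sided: 28 per arm needed; 23 per arm gives 0.836.
- Raw d = 0.84, two-sided: 31 per arm needed; 23 per arm gives 0.796.

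The first three are consistent with 69 and 0.90. The last two are not. All use alpha 0.05 without correction.

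**Power with 69 completers at alpha = 0.05/m.**

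| Model | m = 1 | m = 2 | m = 3 | m = 6 |
|---|---|---|---|---|
| Change score, one-sided | 0.905 | 0.84 | 0.79 | 0.70 |
| Interaction 3 x 2 | 0.906 | 0.85 | 0.81 | 0.73 |
| Baseline-adjusted, two-sided | 0.916 | 0.86 | 0.82 | 0.74 |
| Change score, two-sided (not consistent with 69) | 0.84 | 0.75 | 0.70 | 0.60 |

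Here m = 2 stands for the two primary outcomes on one contrast, m = 3 for the three group contrasts within one outcome, and m = 6 for both together. The interaction is an omnibus test across the three groups, so for that row m = 2 is the most natural reading.

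**The case against.** The trial calls itself exploratory and is non-randomised. Sizing on one contrast at nominal alpha and correcting the comparisons afterwards is common, and it errs on the safe side for false positives: the price is power, not validity. An article may also leave the exact family and the sidedness to a fuller document. All of this lowers the severity. It does not reconcile a stated 0.90 with a blanket correction that the same article announces.

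Three stronger readings are tempting, and the documents support none of them.

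- A reader might infer that corrected power is at most 0.82 and as low as 0.50. The upper figure belongs to three comparisons; correcting for the two primary outcomes alone leaves 0.84 to 0.86. The lower figure needs twelve comparisons (3 contrasts x 2 outcomes x 2 times) in a two-sided change-score model, which has only 0.84 power with no correction at all. It mixes two separate shortfalls.
- A reader might infer that 69 can only come from a one-sided test. The 3 x 2 interaction gives the same total, and section 2.4 does not state sidedness.
- A reader might infer that no analysis keeps 0.90 after correction. If f = 0.21 is assumed to hold across all three time points, the 3 x 3 interaction has 0.905 power at 0.05/3 with 69 completers. That is not how 69 was obtained (it would have given N = 55), but it rules out the universal claim. Likewise, if all 84 recruits completed (28 per arm), the baseline-adjusted test would have 0.924 power over two comparisons and 0.898 over three, although the protocol itself plans for 20% loss.

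**Conclusion.** The inconsistency holds: 0.90 is the power of an uncorrected test, while the protocol says its tests will be corrected. The size of the loss depends on the family, which is not stated. Under the models consistent with 69, and with 23 completers per arm, power is about 0.84 to 0.86 for two comparisons, 0.79 to 0.82 for three and 0.70 to 0.74 for six. With three comparisons the type II error is thus about 0.18 to 0.21 instead of 0.10.

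A second, separate point is that section 2.4 words its target as a difference in mean change. A two-sided test of that difference, with d = 0.84 and r = 0.55, has only about 0.84 power at 23 per arm before any correction. Which test underlies the 69 therefore needs to be stated.

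These figures take the assumed effect and correlation as given. The inconsistency itself is certain; the magnitude is conditional on the assumed family and model. Severity: moderate.

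**What to change.** In section 2.4, name the test and its sidedness, define the Bonferroni family for the primary outcomes (which contrasts, outcomes and time points it covers), and restate power for 69 completers at the corrected alpha. For example, a two-sided baseline-adjusted test over the three group contrasts has about 0.82.

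Alternatively, before any outcomes are seen, designate A-MR against NT on TRIG at T3, two-sided and baseline-adjusted, as the single first test at 0.05. It has about 0.92 power at 69 completers. The other primary contrasts are then tested only if it succeeds, in a fixed order or with a correction among themselves. If they were to be tested whatever its result, the first test could not keep the whole 0.05 and all of them would have to share the correction. Section 2.6 would need matching words. This is one option among several.

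Either way the change is to wording and no further participants are needed. The cost is a less favourable stated power under the first option, or later tests that depend on the first under the second.

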**Method:**

The outlined protocol is a three-arm, non-randomized controlled trial focused on reducing normal and pathological grief symptoms, comparing the effectiveness of Ayahuasca-assisted MR therapy (A-MR), MR therapy alone (MR) and No Treatment (NT). At least 69 people who lost a first-degree relative during the prior year, and with a Texas Revised Inventory of Grief score up 39 (TRIG ≥ 40), will participate in the trial. Participants will be allocated to an A-MR (n ≥ 23), MR (n ≥ 23) or NT (n ≥ 23) group. Those from the A-MR and MR therapy groups will undergo a therapeutic process involving 9 sessions of online psychotherapy. In addition, the A-MR condition involves 2 group sessions of ayahuasca. The primary outcomes will be normal and pathological grief severity as measured by the TRIG and Traumatic Grief Inventory Self-Report (TGI-SR), administered at baseline, post-treatment, and 3-month follow up. Measures of quality of life, post-traumatic growth, meaning-made, psychological flexibility, and self-belief consistency will be also included. In addition, subjective effects of ayahuasca and acceptance-avoidance promoting effects will be assessed following ayahuasca administration. Finally, we will analyze the potential mediating effect of meaning-made, psychological flexibility and self-belief consistency in grief symptoms (as measured by the TRIG and TGI).

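### Recruiting 84 with 20% drop-out leaves about 67 participants, not the 69 the plan needs; 84 covers drop-out of at most 17.9%

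*Protocol article*

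**What the plan says.** Section 2.4 (Sample size) of the protocol article gives the requirement, the expected loss and the recruitment target in one sentence: "a total sample of 69 participants is needed, but as drop-out rate of 20% were considered, 84 participants will be recruited". The calculation behind the 69 is described just before it: "Sample size with power of 0.90 and an alpha of 0.05 was calculated using pwrss R package version 0.3.1". Its inputs are a Cohen's "d (0.84) for the study group between the baseline and the 15^th^-day-post-treatment assessment", taken from an earlier observational study, and a correlation of 0.55 between TRIG measurements. They are applied to a difference of 9.4 TRIG points in mean change between the ayahuasca-assisted arm and the untreated arm.

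The Method part of the Abstract repeats the total ("At least 69 people who lost a first-degree relative during the prior year") and gives the split: "Participants will be allocated to an A-MR (n ≥ 23), MR (n ≥ 23) or NT (n ≥ 23) group". So 69 corresponds to 23 in each of three arms, and 84 to 28 in each if the arms are equal. The article gives no other drop-out rate and no other derivation of 84.

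**The concern.** A drop-out rate is a share of the people recruited. To finish with a required number after losing 20%, that number has to be divided by 0.80. The step from 69 to 84 is smaller than this division gives, so the recruitment target does not provide the allowance that the sentence claims.

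What is at stake is the accuracy of the sample-size statement. Section 2.6 (Data analyses) allows intent-to-treat and/or completer strategies, and repeated-measures ANOVA and/or linear mixed models. In a completer analysis, or a standard repeated-measures ANOVA on complete cases, the number remaining after drop-out is the number that determines power. A reader who takes section 2.4 at its word would expect 69 people in such an analysis at 20% loss. The plan's own figures give about 67.

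**Working it through.** **Inputs.** From section 2.4: required total 69, drop-out 20%, recruitment target 84, d = 0.84, correlation r = 0.55, power 0.90, alpha 0.05 (sidedness not stated). From the Abstract: three arms of at least 23.

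**1. Reproducing 84.**
- Add 20% per arm: 23 × 1.2 = 27.6, rounded up to 28; 28 × 3 = 84. This matches exactly.
- Add 20% to the total: 69 × 1.2 = 82.8, rounded up to 83. This does not match.
- Divide by the retained share, per arm: 23 / 0.80 = 28.75, rounded up to 29; 29 × 3 = 87.
- Divide by the retained share, on the total: 69 / 0.80 = 86.25, rounded up to 87.

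Of these four routes, only the per-arm multiplication gives 84.

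**2. What 84 leaves at 20% drop-out.**
- Total: 84 × 0.80 = 67.2, which is 1.8 below 69.
- Per arm: 28 × 0.80 = 22.4, below 23.
- Largest drop-out at which 69 remain: 1 − 69/84 = 15/84 = 17.9%.
- For comparison, 87 × 0.80 = 69.6, which meets 69.

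**3. Chance variation around the expected number.** If each participant drops out independently with probability 0.20 (an assumption), the probability that at least 69 remain is about 0.37 with 84 recruits and about 0.63 with 87.

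**4. Reproducing 69, so as to size the loss of power.** The article does not print its formula. One reconstruction gives 69:
- Convert d to the change-score scale: 0.84 / √(2(1 − 0.55)) = 0.84 / √0.90 = 0.885.
- Two-sample t-test, one-sided alpha 0.05, power 0.90: 23 per arm, hence 69 for three arms.

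Power for this comparison, with equal arms and d = 0.885:

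| Per arm | Total over three arms | One-sided power |
|---|---|---|
| 23 | 69 | 0.905 |
| 22.4 | 67.2 | 0.898 |
| 22 | 66 | 0.893 |

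The row that belongs to the expected retention is 22.4 per arm: a loss of 0.905 − 0.898 = 0.007, about 0.7 percentage points. The last row corresponds to 66 completers, so it should not be attached to the expected 67.

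**The case against.** The best defence is that the gap is too small to matter. Section 2.6 calls the trial exploratory, and the effect size is borrowed from the before-after change in one observational study. Its uncertainty far outweighs two participants. If linear mixed models are used, someone lost between post-treatment and the 3-month follow-up still contributes to the post-treatment comparison on which the sample size rests. All of this is fair and limits the weight of the point. It does not make the sentence correct, and a completer analysis, which the plan permits, would bear the whole shortfall.

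A second defence reads the 20% as a customary add-on to the required number. That would explain 84, but the text calls it a drop-out rate, and that rate applied to 84 leaves 67. The explanation also remains an inference: the article does not show how 84 was obtained.

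Three stronger readings are tempting, and the article does not support them:

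- **That the target contradicts the Abstract's minimum of 23 per arm.** The Abstract speaks of people taking part and being allocated, not of people completing. Recruiting 84 at 28 per arm satisfies it. The conflict lies within section 2.4 alone.
- **That the trial is bound to miss 69.** The 67.2 is an expected value. Under independent drop-out at 20%, 84 recruits still yield 69 or more with probability about 0.37.
- **That this error is what brings power below 0.90.** Sidedness is not stated, so the one-sided model is a reconstruction. Even under it, power at the expected retention is 0.898, which is 0.90 to two decimals. Under a two-sided test with the same inputs, power is about 0.84 already at 23 per arm, before any loss. That is a separate question and should not be counted here.

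**Conclusion.** The point holds as a small arithmetic error in section 2.4. Recruiting 84 does not allow for 20% drop-out from a required 69: it leaves about 67 (22.4 per arm) and covers at most 17.9%. This follows from the article's own three figures and needs only the ordinary meaning of a drop-out rate, plus equal arms for the per-arm figure.

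The size is about two completers, or three recruits (87 − 84). The power loss of about 0.7 points depends on the one-sided change-score reconstruction and should be quoted only with that label. The cause is best described as consistent with multiplying by 1.2 per arm, not as established. Nothing here threatens the validity of the trial.

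**What to change.** Revise the sentence in section 2.4 in one of these ways:

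1. Keep 84 and state that it preserves 69 participants for drop-out of up to about 17.9%.
2. Keep 84 and the 20% rate, state that about 67 participants (22.4 per arm on average) are then expected to remain, and restate power for that number, naming the test and whether it is one- or two-sided.
3. If the 20% allowance is to be kept in full, change the target to 87 (29 per arm).

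The first two cost one sentence and no extra participants. The third costs three more recruits.
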